# Effect of ice water injection toward the duodenal papilla for preventing post-ERCP pancreatitis: study protocol for a multicenter, single-blinded, randomized controlled trial (EUTOPIA study)

**DOI:** 10.1186/s12876-022-02462-z

**Published:** 2022-08-12

**Keywords:** ERCP, PEP, Post-ERCP pancreatitis, Ice water

## Abstract

**Background:**

Endoscopic retrograde cholangiopancreatography (ERCP) is an essential procedure in the diagnosis and treatment of biliopancreatic diseases. The most common adverse event of ERCP is post-ERCP pancreatitis (PEP), which can sometimes be severe. Our previous study suggested that injecting ice water at the end of ERCP suppressed PEP, and we decided to investigate this effect in a multicenter randomized controlled trial.

**Methods:**

This study is being conducted at eight hospitals in Japan starting in April 2022. Patients undergoing ERCP will be randomized to ice water group and control group. In the ice water group, 250 ml of ice water is injected toward the papilla at the end of ERCP. The next morning, a physical examination and blood tests are performed to evaluate for the development of pancreatitis. The goal is to have 440 cases in each group.

**Discussion:**

The main cause of PEP is thought to be papilla edema. Cooling the papilla, as everyone naturally does at the time of a burn, is expected to prevent its inflammation and edema. Various methods to suppress PEP have been reported, but so far none of them are reliable. The method we have devised is very simple, easy, and safe. We hope that our study will change the world's ERCP common practice.

*Trial registration*:UMIN000047528. Registered 20 April 2022, https://center6.umin.ac.jp/cgi-open-bin/ctr_e/ctr_view.cgi?recptno=R000053209

## Background

Endoscopic retrograde cholangiopancreatography (ERCP) is indispensable for the diagnosis and treatment of biliopancreatic diseases; post-endoscopic retrograde cholangiopancreatography pancreatitis (PEP) is the most problematic procedure-related adverse event. The incidence of PEP is approximately 3.5–9.7%, with severity and mortality rates of 0.04–0.2% and 0.1–0.7%, respectively [1]. Risk factors for PEP include sphincter of Oddi dysfunction (SOD), female sex, history of pancreatitis, history of PEP, difficulty in bile duct cannulation, insertion of a guidewire into the pancreatic duct, and contrast injection into the pancreatic duct [1]. The main cause of PEP is thought to be papillary edema associated with the procedure. Endoscopic techniques, such as prophylactic pancreatic stenting [2–4], wire-guided cannulation [5, 6], and the use of rotatable catheters [7], have been reported to be effective methods for preventing PEP; however, they are not reliable. Various drugs have been studied to suppress papillary edema, but currently, none has been shown to be useful except nonsteroidal anti-inflammatory drugs (NSAIDs) suppositories [8–10]. Prophylactic administration of NSAIDs suppositories into the rectum prior to ERCP has been reported to significantly reduce the incidence of PEP [11–13] and is now widely used. However, NSAIDs are contraindicated in patients with renal failure, aspirin asthma, gastric ulcers, in the elderly, or in patients with allergies.

For prevention of PEP, we are investigating a new and simple method that can be performed by anyone. Cooling is widely known to be effective in treating acute inflammation and edema in burns. Similarly, we hypothesized that cooling the papilla of Vater would help reduce papillary edema. Our previous single-center prospective study suggested that cooling the papilla with ice water may reduce the incidence of PEP by 4% [14]. However, the results of this trial are uncertain because it is only a single-arm prospective study. This uncertainty has led to a call for randomized controlled trials to validate the results.

### Objectives

#### Primary objective

To determine the effect of ice water injection into the papilla of Vater on the incidence of PEP.

#### Secondary objective

This study aims to determine the efficacy of ice water injection into the papilla of Vater on the incidence of moderate-to-severe PEP and other adverse events.

## Methods/design

### Trial design

EUTOPIA is a multicenter, randomized, controlled, patient-blinded, superiority trial with two parallel groups.

### Participants

#### Study settings

The EUTOPIA study is being conducted in eight hospitals (two universities and six general hospitals) in Japan.

#### Eligibility criteria

Figure 1 shows the patients’ eligibility criteria and Fig. 2 shows the study protocol.

**Fig. 1 Fig1:**
[figure not shown]
Eligibility criteria and grouping

**Fig. 2 Fig2:**
[figure not shown]
Study protocol. ^※^Baseline variables: age, sex, ECOG-PS, ASA-PS, history of acute or recurrent pancreatitis, serum total bilirubin level before ERCP, serum amylase level before ERCP, ERCP indication, and presence of SOD, cholangitis, pancreatic duct obstruction at the head of the pancreas. ^Primary outcome: presence of PEP. ^#^Secondary outcomes: presence of PEP in cases of difficult cannulation, PEP by various ERCP procedures, PEP by the presence of pancreatic duct cannulation and pancreatography, PEP by cannulation time, moderate and severe PEP, and PEP by high-risk factors for PEP

#### Inclusion criteria

Patients over 20 years of age with native papilla who undergo ERCP are eligible.

#### Exclusion criteria

Patients fulfilling one or more of the following criteria are excluded:

(1) Eastern Cooperative Oncology Group Performance Status 4; (2) age younger than 20 years; (3) non-native papilla; (4) prediction of papilla inaccessibility; (5) postoperative reconstructed intestinal tract excluding Billroth I reconstruction; (6) presence of acute pancreatitis; (7) presence of chronic pancreatitis; (8) presence of pancreatic head cancer with occlusion of the main pancreatic duct; (9) inability to provide written informed consent; and (10) patients deemed inappropriate for the trial.

### Interventions

A diagram of the study protocol is shown in Fig. 2. All patients are fasted on the day of ERCP. NSAIDs suppositories are not administered. During the examination, the heart rate, non-invasive blood pressure, and oxygen saturation are monitored, and pain is reduced using sedatives and analgesics.

The patients are randomized into the ice water or control group prior to ERCP.

ERCP is performed using a side-viewing duodenoscope (TJF-260 V or TJF-Q290V; Olympus Medical Systems Co. Ltd., Tokyo, Japan) in a standard manner.

In the ice water group, a total of 250 mL of ice water is injected, which is done in five increments using a 50 mL syringe, toward the papilla at the end of ERCP. Duodenal fluid is aspirated after each 50-mL injection of ice water, and the injection is repeated.

During ERCP, the total examination time (from insertion of the scope to its removal), procedure time (from the start of cannulation to the end of treatment), time required for cannulation, and the number of papillary contacts, etc. are recorded on the findings form (Fig. 3).

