#### Secondary outcome measures

The secondary outcomes are as follows: (1) incidence of PEP in cases of difficult cannulation, (2) incidence of PEP by various ERCP procedures, (3) incidence of PEP by the presence of pancreatic duct cannulation and pancreatography, (4) incidence of PEP by cannulation time, (5) incidence of moderate and severe PEP, (6) incidence of PEP by high-risk factors for PEP, and (7) incidence of other complications.

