### Assigning interventions

#### Allocation

Randomization is centralized, web-based, and accessible 24 h a day; it is balanced (1:1) and stratified by center and the cause of the indication for ERCP [for bile duct cannulation or otherwise (for pancreatic duct and both bile and pancreatic ducts cannulation)].

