#### Blinding

The allocation result is unknown to the patient because knowing it may affect the appearance of abdominal pain, which predicts the onset of PEP.

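### Patients are randomised before ERCP although the arms differ only at its end, and nothing stated keeps the arm from the endoscopist during the operator-dependent steps

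*Protocol article*

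**What the plan says.** Under Interventions, the protocol article fixes the order of events: "The patients are randomized into the ice water or control group prior to ERCP". In the same section the ice water is injected "toward the papilla at the end of ERCP", and the abstract agrees: "250 ml of ice water is injected toward the papilla at the end of ERCP". The control group has no corresponding step, so by design the arms differ only once the ERCP is otherwise finished.

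On blinding, Trial design reads: "EUTOPIA is a multicenter, randomized, controlled, patient-blinded, superiority trial with two parallel groups". The Blinding section says: "The allocation result is unknown to the patient because knowing it may affect the appearance of abdominal pain". No other person is named as blinded, and no section says when the endoscopist learns the arm.

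Under Allocation: "Randomization is centralized, web-based, and accessible 24 h a day". The two stratification factors are centre and the indication for ERCP. The secondary outcomes include "incidence of PEP by the presence of pancreatic duct cannulation and pancreatography", together with PEP by difficult cannulation, by type of procedure and by cannulation time.

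**The concern.** Between randomisation and injection lies the whole ERCP, and what the operator does there affects the primary outcome. The Background names difficult bile duct cannulation, a guidewire in the pancreatic duct and pancreatic contrast as risk factors. It names pancreatic stenting, wire-guided cannulation and rotatable catheters as preventive techniques. Definitions adds pre-cut, pancreatic sphincterotomy and papillary balloon dilation. The article withholds NSAID suppositories, requires fasting and names the duodenoscopes, but otherwise says only that ERCP follows standard practice. An operator who knows the arm could be more or less persistent at cannulation, or quicker to use one of these techniques, without breaching anything written.

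Two things are at stake. The first is the primary comparison: a difference in technique between arms would be counted as an effect of ice water, or would hide one. The second is the set of secondary analyses by difficult cannulation, procedure, pancreatography and cannulation time. These groups form after randomisation, so an operator who knows the arm can influence who falls into them. Difficult cannulation also rests on contact counts and times noted during the procedure.

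**Working it through.** **1. Sequence of events, from the article**

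| Event | Timing | Section |
|---|---|---|
| Randomisation | before ERCP | Interventions |
| Cannulation, pancreatography, pre-cut, dilation, sphincterotomy | during ERCP | Interventions; Definitions |
| Ice water (one arm only) | end of ERCP | Interventions; Abstract |
| Person stated to be blinded | patient only | Trial design; Blinding |

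The article gives no reason for allocating at the start. Centre and indication are both known before ERCP, so stratification works equally well if the allocation is called or disclosed later.

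**2. The plan's own sample size**

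Inputs (Sample size): 10% vs 5%, two-sided α 0.05, power 0.80, 1:1. Pooled normal approximation, with mean proportion 0.075:

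n = [1.960 × √(2 × 0.075 × 0.925) + 0.842 × √(0.10 × 0.90 + 0.05 × 0.95)]² / 0.05² = (0.730 + 0.312)² / 0.0025 ≈ 434.4, rounded up to 435.

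This reproduces the stated 435 per arm. The timing of allocation does not change it.

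**3. What a shift in technique could do**

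The documents give no figure for a change in operator behaviour, so every shift here is an assumption. Suppose knowing the arm changes practice in a fraction f of one arm, and that these patients' PEP risk goes from 15% to 7%. The arm's rate then moves by f × 8 points:

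- f = 10%: 0.10 × 8 = 0.8 points, or 0.8/5 = 16% of the targeted 5-point difference.
- f = 2.5%: 0.025 × 8 = 0.2 points, or 0.2/5 = 4% of it.

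The planned test is the two-tailed Fisher exact test at 5%. Its rejection region was enumerated in full for 440 per arm and weighted by the two binomial distributions.

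| Scenario | Control vs ice water | Result |
|---|---|---|
| True effect, no shift | 10% vs 5% | power 77.7% |
| True effect, control arm shifts 0.2 | 9.8% vs 5% | power 74.5% |
| True effect, control arm shifts 0.8 | 9.2% vs 5% | power 63.7% |
| No effect, no shift | 10% vs 10% | significant for ice water 1.9% |
| No effect, ice water arm shifts 0.2 | 10% vs 9.8% | significant for ice water 2.4% |
| No effect, ice water arm shifts 0.8 | 10% vs 9.2% | significant for ice water 4.7% |

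The nominal rate on the ice water side is 2.5%. The smaller shift stays just below it because the Fisher test is conservative; the larger shift exceeds it.

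**The case against.** The strongest reply is that the article dates randomisation and not disclosure to the operator. The study diagram and findings form are not visible here, and a fuller protocol may conceal the arm until the injection. A reader might infer that the endoscopist certainly knows the arm throughout; the text does not say so. It remains the natural reading of early allocation in a trial that blinds only the patient, and nothing in the article contradicts it.

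A reader might also infer that every driver of PEP is open to influence. Definitions lists female sex under 60, suspected sphincter of Oddi dysfunction, recurrent pancreatitis and previous PEP, which no operator can alter. The point is confined to procedural steps.

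The size is assumed. Going from 15% to 7% is a relative reduction of 8/15 = 53% from technique alone, more than the 50% assumed for ice water, so the 0.8-point case is a generous one. At 0.2 points the effect is small. The net direction is unknown as well. The calculation shows what bias could do, not that it occurs.

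Nor are the procedural subgroups invalid as they stand. Ice water given at the end cannot cause a difficult cannulation, so they are distorted only if the operator acts on, or records differently because of, the known arm.

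Finally, patient-only blinding is openly declared, and recorded times and papillary contacts would let an imbalance be seen. Both are true. Declaring the design does not remove the bias, and adjusting for recorded factors would not fully cure it.

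**Conclusion.** The point stands as a potential and avoidable performance bias; the documents do not demonstrate an actual one. Early allocation with patient-only blinding leaves a route by which knowledge of the arm can reach the primary outcome and the subgroups by difficult cannulation, procedure, pancreatography and cannulation time. No section closes it.

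Within the assumed range of 0.2 to 0.8 points, the loss is 3.2 to 14.0 percentage points of power (77.7% less 74.5% or 63.7%), or a gain of 0.5 to 2.8 points in the false-benefit rate (2.4% or 4.7% less 1.9%), depending on which arm shifts. These figures rest on the plan's 10% and 5%, full enrolment of 440 per arm, and a shift that the documents neither support nor exclude.

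This should be fixed, because the remedy is cheap and the bias could not be reliably removed in the analysis.

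**What to change.** Amend the Interventions section so that, for patients not yet enrolled, the web allocation is obtained, or revealed to the operator, only after the last therapeutic step and once the procedural fields of the findings form are entered. Total examination time is the exception, since it ends with scope removal. If the fuller protocol already conceals the arm until that point, the article need only say so.

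Recruitment had begun when the article appeared. Analyse patients already enrolled as randomised, add a sensitivity analysis by enrolment before or after the amendment, and compare the procedural factors between arms.

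The cost is a protocol amendment, a short pause with the scope in place, and ice water prepared but unused in about half the cases under 1:1 allocation. The web system is already open round the clock, and neither the sample size nor the stratification changes.

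Two limits apply. The operator must still learn the arm at the injection, so this delays that knowledge and does not create operator blinding. It also does not blind whoever assesses PEP. The exclusion of inadequately treated patients from the full analysis set is a separate matter that this change does not settle.

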**Fig. 3 Fig3:**
[figure not shown]
Findings form

The patient’s symptoms are monitored after ERCP. The next morning, medical examination is performed to determine if the patient meets the criteria for PEP, and if the patient experiences abdominal pain, blood tests may be performed at the discretion of the physician in charge.

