### Outcomes

#### Primary outcome measure

The primary outcome is the incidence of PEP in the ice water and control groups. PEP is defined as the onset of abdominal pain within 24 h of ERCP and elevation of serum amylase and lipase levels to at least three times the upper limit of normal based on the Cotton criteria[15].

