### Definitions

The severity of PEP is classified as follows, modifying Cotton criteria: mild disease, which requires 2–3 days of fasting; moderate disease, which requires 4–10 days of fasting; and severe disease, which requires 11 or more days of fasting[15]. In addition to the above, patients with necrosis or pseudocyst formation or those who underwent percutaneous drainage or surgery were defined to have severe disease[15].

Difficult cannulation is defined as contact with the papilla more than five times, cannulation time more than 5 min, and unintentional pancreatic duct cannulation more than two times [1]. Definition and severity of cholangitis prior to ERCP; in accordance with Tokyo Guidelines 2018[16]. ERCP trainee is defined as a physician with less than 200 cases of ERCP experience. The following factors have been identified as risk factors for PEP: (1) pre-cut sphincterotomy, (2) endoscopic pancreatic sphincterotomy, (3) endoscopic papillary balloon dilation, (4) difficult cannulation cases, (5) pancreatography, (6) female patients under 60 years old, (7) suspected SOD, (8) history of recurrent pancreatitis, and (9) history of PEP[1].

Regarding other ERCP comorbidities, hemorrhage is defined as hematemesis or a drop in hemoglobin concentration of > 2 g/dL and perforation as the presence of air or intestinal contents beyond the intestinal tract[17]. Other comorbidities and their severity follow the ASGE guidelines[17].

The ice water used in this study is defined as 250 mL of chilled water in a refrigerator with ten ice cubes made with an ice machine.

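### The Abstract and the Methods give different rules for the blood tests that the primary endpoint needs, and the Methods rule leaves testing to a physician for whom no masking is described

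*Protocol article*

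**What the plan says.** All references are to the protocol article.

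- **Outcome definition (Primary outcome measure).** Two components must both be present. The first is abdominal pain that begins in the 24 h following the procedure. The second is "elevation of serum amylase and lipase levels to at least three times the upper limit of normal".
- **Blood tests, Abstract (Methods paragraph).** "The next morning, a physical examination and blood tests are performed to evaluate for the development of pancreatitis". No condition is attached.
- **Blood tests, body of the article (Interventions, paragraph after Fig. 3).** Symptoms are monitored after ERCP, and a medical examination the next morning decides whether the PEP criteria are met. Then: "if the patient experiences abdominal pain, blood tests may be performed at the discretion of the physician in charge".
- **Blinding (Trial design; Blinding).** The trial is described as patient-blinded, and the reason is given: "The allocation result is unknown to the patient because knowing it may affect the appearance of abdominal pain". No masking of the treating physician or of an outcome assessor is described.
- **Timing of allocation (Interventions).** "The patients are randomized into the ice water or control group prior to ERCP".
- **Analysis (Statistical analysis).** The PEP percentage uses the number of full analysis set (FAS) cases as denominator, and the arms are compared by a two-tailed Fisher's exact test at 5%.

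**The concern.** The enzyme criterion can be met only by a patient whose blood is drawn. Under the Abstract's rule, every patient has the values. Under the Methods rule, a patient with pain may or may not have them, and one physician's judgement decides. A step that determines whether an event can be recorded is therefore optional.

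Two things are at stake. If testing is incomplete to the same degree in both arms, true cases are lost, the observed event rates fall and power falls with them. If testing is less complete in one arm, the comparison itself is biased. The second possibility is open because only the patient's blinding is described. The Blinding section accepts that knowing the allocation can influence reported pain, and the same reasoning applies to whoever asks about pain and decides whether to test. An enzyme sample that was not taken in time cannot be recovered at the analysis stage.

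**Working it through.** **Step 1. The two rules side by side.**

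| | Abstract | Methods, after Fig. 3 |
|---|---|---|
| Who is tested | patients, no condition | patients with abdominal pain |
| Obligation | tests are performed | tests may be performed |
| Who decides | nobody, it is routine | physician in charge |

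Both cannot be the operating rule at the eight hospitals.

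**Step 2. Which patients matter.** PEP needs pain and enzymes together. A patient without pain cannot have PEP whatever the enzymes show, so leaving pain-free patients untested does not change the primary outcome. The exposed group is patients with pain who are not tested.

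**Step 3. The plan's own figure.** Inputs from the Sample size section: 10% versus 5%, two-sided α = 0.05, power 0.80, 1:1. Normal approximation with pooled variance under the null, mean rate 0.075:

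n = [1.960·√(2·0.075·0.925) + 0.842·√(0.10·0.90 + 0.05·0.95)]² / 0.05² = (0.7301 + 0.3121)² / 0.0025 = 434.4, rounded up to **435**.

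This reproduces the stated 435 per arm, so the sample size is not in dispute. At the planned 440 per arm, exact power of the planned Fisher test is 77.7% (80.5% by the normal approximation).

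**Step 4. Effect of incomplete testing.** Observed rate = true PEP rate × share of true PEP cases that are tested. The documents give no such shares, so those below are assumptions. Untested cases are taken as non-events. Probabilities come from exact enumeration of the two-sided Fisher test at 440 per arm.

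*No true effect, 10% in both arms:*

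| Share tested, control / ice water | Observed rates | Observed risk ratio | P(significant in favour of ice water) |
|---|---|---|---|
| 100% / 100% | 10.0% / 10.0% | 1.00 | 1.9% |
| 90% / 85% | 9.0% / 8.5% | 0.94 | 3.5% |
| 90% / 80% | 9.0% / 8.0% | 0.89 | 6.1% |
| 90% / 70% | 9.0% / 7.0% | 0.78 | 16.2% |

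The nominal one-directional rate is 2.5%. Fisher's test is conservative, hence 1.9% in the first row.

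*True effect 10% versus 5%, same share tested in both arms:*

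| Share tested | Observed rates | Power |
|---|---|---|
| 100% | 10.0% / 5.0% | 77.7% |
| 90% | 9.0% / 4.5% | 72.3% |
| 80% | 8.0% / 4.0% | 66.3% |
| 70% | 7.0% / 3.5% | 59.6% |

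*Gap in the other direction:* with 90% of control cases and all ice water cases tested, a true 10% versus 5% appears as 9% versus 5%, and power is 59.8%. A gap in testing can hide a benefit as well as create one.

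**The case against.** The strongest reply is that the defect is one of wording. The Methods never say that blood is drawn only in patients with pain. The next-morning examination is meant to establish whether the PEP criteria are met, which is impossible without enzymes, and the Abstract says that blood tests are done. The discretionary sentence could then mean additional tests. Figs. 2 and 3 are not shown, and the full protocol may contain a schedule. This reading is possible but not the natural one, and the contradiction between the two statements stands either way.

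Several stronger readings are tempting and should not be adopted:

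- *The physician is unblinded.* A reader might infer this because masking is stated for the patient alone and allocation precedes ERCP. The documents do not say who examines the patient the next morning or what that person knows.
- *Untested patients are counted as free of PEP.* This follows from the FAS denominator only if they stay in the FAS. No rule for missing enzymes is stated, and that detail is commonly left to the statistical analysis plan.
- *The trial is biased towards ice water.* Nothing in the documents supports any particular gap in testing or its direction. The shares refer to true PEP cases, that is, patients with pain and enzymes at least three times the limit, so large gaps should not be presumed.
- *Pain starting after the morning visit is missed.* The article states that symptoms are monitored after ERCP, without tying this to the morning visit.
- *Haemorrhage has the same flaw.* That secondary outcome uses a haemoglobin drop, but it can also be met by hematemesis. The point is peripheral.

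**Conclusion.** The point holds as an internal contradiction about how the primary endpoint is ascertained. It is a matter of two stated rules, not of detail left out of a condensed article. If the Methods rule is followed as written, PEP can go unrecorded in patients with pain, and the protocol article describes no safeguard against this differing by arm. Whether it does differ is not shown.

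The size is illustrative. It rests on assumed testing shares, on untested cases staying in the denominator as non-events, and on the plan's own 10% and 5%. Small gaps matter little: 90% versus 85% moves the chance of a false finding for ice water from 1.9% to 3.5%. A ten-point gap roughly triples it to 6.1%, and a twenty-point gap brings it to about 16%. Equal under-testing at 80% costs about 11 points of power (77.7% to 66.3%) with no bias at all. It should be corrected while patients are still being enrolled, because later analysis cannot supply enzyme values that were never measured.

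**What to change.** Reconcile the Abstract with the paragraph after Fig. 3. State that serum amylase and lipase are a mandatory outcome measurement in at least every randomised patient with abdominal pain starting within 24 h of ERCP. Sampling all patients the next morning, as the Abstract describes, also satisfies this; for the primary outcome it adds nothing in pain-free patients, but it leaves no room for discretion.

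State who makes the next-morning PEP assessment and, where existing staffing allows, have it made without knowledge of the allocation.

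The cost is a few more routine blood samples and an amendment during enrolment. Its date should be recorded, so that patients assessed before and after the change can be told apart.
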